### Adherence to interventions

To enhance the validity of the data, participants will return the unused capsules and bottles at each follow-up visit. Unused capsules will be counted and recorded on the appropriate case report form. Participants will be asked about any problems they are having taking their study treatment.

### Concomitant interventions

Some medications are prohibited during the study duration: triptans, tramadol, anxiolytic drugs, other serotonergic agents or antidepressants, as well as hormone replacement therapy. Psychotherapy is also forbidden during the study duration. Medication for diabetes and hypertension is allowed. The rescue intervention in case of a lack of efficacy in the IHT and placebo groups will be fluoxetine 20 mg/day; in the fluoxetine group, the rescue medication will be sertraline 25 mg/day.

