### Aims

The primary aim of the study is to assess the efficacy of individualized homeopathic treatment (IHT) versus fluoxetine and placebo, and fluoxetine versus placebo in peri- and postmenopausal women with moderate to severe depression scored by the 17-item HRSD.

Secondary aims are: (1) to assess the efficacy of IHT versus fluoxetine and placebo, and fluoxetine versus placebo using the BDI and GS’s score; and (2) to determine the safety of IHT versus fluoxetine and placebo, and fluoxetine versus placebo in peri- and postmenopausal women with moderate to severe depression.

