### Types of interventions

After inclusion, patients will be randomly assigned to either one of three groups illustrated in Figure 1: (1) IHT plus fluoxetine dummy-loaded; (2) fluoxetine (20 mg/day) plus IHT dummy-loaded; and (3) fluoxetine placebo plus IHT placebo.

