**Figure 1 F1:**
[figure not shown]
Flow chart of the study groups.

The selection of the individualized remedy will be carried out after the case history by a certified medical doctor, specialized in homeopathy with 18 years’ experience in classical homeopathy. The case history will be based on Hahnemann’s methodology described in paragraphs 83 to 104 of Organon of Medicine, 6th edition. A complete medical history with clinical examination will also be done. All patients will have a full homeopathic case-taking including the collection of all the facts pertaining to the patient which may help in determining the totality of the symptomatology: past and present physical and emotional symptoms, family environment since childhood, stressful life events, marital satisfaction. The symptoms will be organized by hierarchy: mental, general and physical. In the first place, the strategy to choose the individualized remedy will be based on the most characteristic and clear mental symptoms. Secondly, general symptoms will be taken into account. A computerized version of the Synthesis Homeopathic Repertory 9.1 (Radar version 10) will be used to facilitate the prescription. Only one remedy will be prescribed at a time but it could be changed at every follow-up according to the patient’s symptoms.

C-potencies will be provided by Laboratorio Similia (Mexico City) and are manufactured according to the Mexican Homeopathic Pharmacopoeia and Hahnemann’s methodology. Each individualized homeopathic remedy will be prescribed in C-potencies (Appendix 1). Higher initial potencies will be tried, ranging from 30 to 200 C. The factors that influence the selection of the potency will include: clarity of mental symptoms, patient’s vitality and sensitivity, nature and kingdom (source) of medicine, chronicity and presence of any pathological disorder. A single dose of the individualized homeopathic remedy selected will be dissolved in a 60 ml bottle of 30% alcohol-distilled water. Patients will receive 15 drops PO two times per day following agitation for 10 days, plus fluoxetine-dummy loaded prescribed PO daily. A double-dummy technique with matching placebos for each active treatment will be applied, thus both placebos will seem identical to their corresponding *verum* formulations. Follow-up will be at weeks four and six after the first clinical interview.

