### Outcomes

The primary efficacy outcome is the change from baseline in mean total depression score using the 17-item version of the HRSD at weeks four and six. The severity of symptoms will be assessed by a blinded investigator (clinical psychologist) from the JMH. The secondary outcomes are: change from baseline in mean total depression score using BDI (a self-reported scale) at weeks four and six; change from baseline in mean total score of GS at weeks four and six; responder rates (response rate: decrease of 50% or more from baseline score; remission rate: HRSD ≤7). The number and severity of all adverse events and homeopathic aggravations during the study period and 15 days after the final dose will be collected to determine the safety of fluoxetine and homeopathic medicines. An adverse event will be defined as any untoward medical occurrence in a subject without regard to the possibility of a causal relationship. Adverse events will be collected after participants have given consent and enrolled in the study and 15 days after study completion.

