### Statistical analysis

All patients under randomization will be included in the primary efficacy population (intention-to-treat population), regardless whether or not they adhered to the treatment protocol or provided complete data sets. Only patients who withdraw their consent to use their personal data will be excluded from the analysis. The flow of participants through the trial will be presented in a Consolidate Standards of Reporting Trials (CONSORT) diagram.

First, the three groups will be compared in order to verify that there are no significant differences among them at baseline to confirm they are comparable after randomization. Demographic characteristics will be summarized using means and standard deviation for continuous data (that is, age) and relative frequencies for qualitative data (that is, marital status, comorbidities). The baseline demographic characteristics among groups will be compared with the use of the chi square test or by one-way independent measures of analysis of variance (ANOVA) as required.

We will compare: (1) IHT versus placebo; (2) fluoxetine versus placebo; and (3) IHT versus fluoxetine. The main statistical analysis will compare primary and secondary outcome measurements among groups at weeks four and six. The primary outcome (change in mean HRSD score) and secondary outcomes (change in mean BDI and GS scores) among groups at baseline and weeks four and six, will be analyzed by one-way ANOVA to provide a statistical test of whether or not the means of the three groups are all equal. The statistically significant one-way ANOVA result (*P* <0.05) suggests rejecting the global null hypothesis H_0_ (that the means are the same across IHT, fluoxetine and placebo groups). The Bonferroni *post-hoc* test will be used to determine which means differ among the groups. Responder rates will be compared among the groups using the chi square test. Statistical significance will be set at *P* <0.05 level for all analysis. Missing data will be handled by sensitivity analysis.

All patients who received at least one dose of the study drugs will be considered in the safety analysis. Adverse events will be translated to Medical Dictionary for Regulatory Activities terms (MeDRa terms), quantified and compared among the groups using the chi square test. Homeopathic aggravation will be compared among the groups also using the chi square test.

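### Rescue in the IHT and placebo arms is the comparator drug, and response and remission are judged on score alone, so a rescued patient can count as a success of the arm that failed (minor)

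*Protocol article*

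**What the plan says.** - **Rescue.** Protocol article, Concomitant interventions, on two of the three arms: "The rescue intervention in case of a lack of efficacy in the IHT and placebo groups will be fluoxetine 20 mg/day". For the remaining arm it names a different drug: "in the fluoxetine group, the rescue medication will be sertraline 25 mg/day". No criterion, timing or expected frequency is given. The rule stands among others that apply while the study runs, and post-trial care has its own section, so in-trial use is the natural reading.
- **Comparator.** Types of interventions describes the active control as "fluoxetine (20 mg/day) plus IHT dummy-loaded", the same drug and dose as the rescue in the other two arms.
- **Visits.** Types of interventions: "Follow-up will be at weeks four and six after the first clinical interview".
- **Response and remission.** Outcomes: "decrease of 50% or more from baseline score; remission rate: HRSD ≤7". Neither carries a condition on rescue.
- **Who is analysed.** Statistical analysis keeps every randomized patient, "regardless whether or not they adhered to the treatment protocol or provided complete data sets". The one exclusion is: "Only patients who withdraw their consent to use their personal data will be excluded from the analysis". The section on discontinuing or modifying interventions adds that participants are kept in follow-up where possible.
- **Purpose.** The primary aim concerns the efficacy of IHT, which is to be judged "versus fluoxetine and placebo, and fluoxetine versus placebo in peri- and postmenopausal women with moderate to severe depression scored by the 17-item HRSD".

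**The concern.** Each of these statements is ordinary alone. Together they fix an awkward result. A woman in the IHT or placebo arm whose treatment is judged to have failed receives the comparator and stays in follow-up. She is then rated on it and classed by that rating in her allocated arm. If her score has halved, or is 7 or less, she is a responder or remitter of the treatment that was abandoned. The missing-data sentence in Statistical analysis does not catch this, because her score is observed.

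Two contrasts are exposed. Fluoxetine–placebo is drawn towards no difference, and so is IHT–fluoxetine if fluoxetine is truly the better of the two. The Discussion wants the fluoxetine arm to show whether the fluoxetine–placebo difference is as small as some meta-analyses report, and comparator rescue in the placebo arm leans towards that answer. IHT–placebo moves only if rescue, or the gain from it, differs between those two arms.

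**Working it through.** **Inputs from the protocol article**
- HRSD difference 2.7, SD 6.0, at six weeks (Sample size calculation). The stated effect size reproduces: 2.7/6.0 = 0.45.
- 63 per group with 10% drop-out (same section): 63 × 0.9 = 56.7, about 57 per group.
- Antidepressant response about 50% within eight weeks (Background).
- Placebo response or remission about 35% (Discussion).

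**Assumptions, since the article gives no figure**
- Share of the placebo arm rescued: r = 0.1, 0.2, 0.3.
- Rescue starts at the week-4 visit, leaving two of six weeks. With linear gain, a rescued patient obtains g = 2/6 = 1/3 of the 2.7 points by week 6.
- Share of rescued patients credited as responders: the eight-week 50% scaled linearly to two weeks, 0.50 × 2/8 = 0.125. None of them would have responded otherwise.
- Sertraline rescue, where counted, brings the same gain. The share of the fluoxetine arm rescued is rF.

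**Responders at week 6, fluoxetine against placebo**

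Gap = (0.50 + 0.125·rF) − (0.35 + 0.125·r)

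| r | Placebo rate | Gap, rF = 0 | Gap, rF = r/2 | Gap, rF = r | Placebo patients credited (57 × r × 0.125) |
|---|---|---|---|---|---|
| 0.1 | 36.25% | 13.75 | 14.4 | 15 | 0.7 |
| 0.2 | 37.5% | 12.5 | 13.75 | 15 | 1.4 |
| 0.3 | 38.75% | 11.25 | 13.1 | 15 | 2.1 |

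Gaps are in percentage points; without rescue the gap is 50 − 35 = 15.

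**Mean HRSD difference at week 6, fluoxetine against placebo**

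Difference = 2.7 × (1 − r/3) + 2.7 × rF/3

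Power is for a two-sample t test with SD 6, 57 per group and two-sided alpha 0.05/3 (Bonferroni, three pairs). Without rescue: 2.70 points, power 49.1%.

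| r | rF = 0 | rF = r/2 | rF = r |
|---|---|---|---|
| 0.1 | 2.61 (46.0%) | 2.655 (47.5%) | 2.70 (49.1%) |
| 0.2 | 2.52 (42.8%) | 2.61 (46.0%) | 2.70 (49.1%) |
| 0.3 | 2.43 (39.8%) | 2.565 (44.4%) | 2.70 (49.1%) |

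The 49.1% starting value comes from the sample size and the pairwise alpha, not from rescue. It is a separate matter.

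**IHT against placebo**, taking a true difference of 2.7: difference = 2.7 − 2.7 × (1/3) × (rP − rI). Equal rescue in both arms leaves 2.70; 30% placebo and 10% IHT rescue gives 2.7 − 0.9 × 0.2 = 2.52.

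**IHT against fluoxetine.** The article states no expected difference. If IHT were no better than placebo, the fluoxetine–placebo tables would apply with the IHT arm in place of placebo.

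**The case against.** The strongest reply is that this is a choice of estimand, not an error. Analysing all scores by allocated arm is a legitimate treatment-policy approach. If it is acceptable for HRSD change, it can be applied to dichotomies built from the same scores. Rules for rescued patients are often left to an analysis plan, which is not at hand. Part of this stands: the all-scores HRSD analysis should remain primary, and the absence of further detail is not the complaint. What remains is that the article itself fixes the rescue drug, the score-only definitions and the inclusion rule, and following them can report a treatment failure as that arm's success.

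The reply on timing also has force. Rescue has no stated time, the only scheduled follow-ups are weeks 4 and 6, and the Blinding section keeps HRSD scores sealed, so they cannot trigger rescue. Rescue begun at week 4 touches only week 6; rescue begun at week 6 touches neither rating. Rescue between visits is not excluded, but no scheduled visit corresponds to it.

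Finally, sertraline rescue must be counted for responders as well as for HRSD. With it, the loss is smaller and can be nil.

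**Conclusion.** The point holds as a minor one. The stated rules allow a rescued patient to be counted as a responder or remitter of the arm that failed. The likely effect is about one to two of 57 placebo patients credited. The responder gap loses 1.3 to 3.8 points without the sertraline offset, 0.6 to 1.9 with half as many fluoxetine patients rescued, and nothing with equal rescue and gain. The HRSD difference loses about 0.1 to 0.3 points without the offset and at most about 0.1 with it. All of this rests on assumed rescue rates, week-4 timing, linear gain and equal benefit from sertraline.

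A reader might infer more, and the article does not support it:
- **That rescue hides any real fluoxetine advantage.** With equal rescue and gain in both arms there is no dilution.
- **That the responder gap could vanish.** That needs, for example, 30% of the placebo arm rescued with half of them responding (35% + 0.3 × 50% = 50%). This is the full eight-week rate reached in about two weeks, with no sertraline offset.
- **That the primary intention-to-treat analysis is unsound.** It is not.
- **That week 4 is compromised.** Nothing stated shows rescue before that visit.

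**What to change.** 1. In all three arms, count a patient as a non-responder and non-remitter at every visit after rescue begins. A rating taken at the visit where rescue starts, before the first rescue dose, still counts as it stands.
2. Take the date of rescue from study or medical records; Data collection already names medical records as a source.
3. Keep the all-scores HRSD analysis by allocated arm as primary. Add one prespecified supplementary HRSD analysis that sets post-rescue scores aside and models the data up to rescue, instead of carrying the last score forward.

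The clinical rescue rule stays with the investigators.

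**Cost.** A few sentences of analysis wording and the retrieval of rescue dates. Recruitment began in March 2012, so extra ratings before rescue cannot be obtained for women already treated; the fix does not depend on them.

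**Downsides.** A rescued patient who would have responded anyway is counted as a failure, and the supplementary analysis rests on assumptions that the data cannot test.

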### Participant retention

Plans to promote participant retention and complete follow-up will include: scheduling appointments and contacting patients by telephone.

### Outcomes

The primary efficacy outcome is the change from baseline in mean total depression score using the 17-item version of the HRSD at weeks four and six. The severity of symptoms will be assessed by a blinded investigator (clinical psychologist) from the JMH. The secondary outcomes are: change from baseline in mean total depression score using BDI (a self-reported scale) at weeks four and six; change from baseline in mean total score of GS at weeks four and six; responder rates (response rate: decrease of 50% or more from baseline score; remission rate: HRSD ≤7). The number and severity of all adverse events and homeopathic aggravations during the study period and 15 days after the final dose will be collected to determine the safety of fluoxetine and homeopathic medicines. An adverse event will be defined as any untoward medical occurrence in a subject without regard to the possibility of a causal relationship. Adverse events will be collected after participants have given consent and enrolled in the study and 15 days after study completion.

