**Methods/design:**

A randomized, placebo-controlled, double-blind, double-dummy, three-arm trial with a six-week follow-up study was designed. The study will be conducted in a public research hospital in Mexico City (Juárez de México Hospital) in the outpatient service of homeopathy. One hundred eighty nine peri- and postmenopausal women diagnosed with major depression according to the Diagnostic and Statistical Manual of Mental Disorders, 4th edition (moderate to severe intensity) will be included. The primary outcome is change in the mean total score among groups on the 17-item Hamilton Rating Scale for Depression after the fourth and sixth week of treatment. Secondary outcomes are: Beck Depression Inventory change in mean score, Greene’s Scale change in mean score, response and remission rates and safety. Efficacy data will be analyzed in the intention-to-treat population. To determine differences in the primary and secondary outcomes among groups at baseline and weeks four and six, data will be analyzed by analysis of variance for independent measures with the Bonferroni *post-hoc* test.

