### Sample size calculation

Sample size calculation was estimated using G*Power (available at the University of Düsseldorf: http://www.psycho.uni-duesseldorf.de/abteilungen/aap/gpower3/). The sample size calculation is based on a previous study protocol for a randomized controlled trial of homeopathy for depression published by Adler *et al.*[21]. We assumed that *verum* treatment is better than placebo by 2.7 ± 6.0 (mean ± standard deviation) HRSD score points after six weeks [21], corresponding to an effect size = 0.45 (largest difference between any two groups to be detected/expected within group standard deviation = diff/de). To detect an effect size = 0.45, in a three-group design (1:1:1), using F-Test, with a 5% risk of type 1 error (α) and 83% power, 63 patients per group are required considering also a 10% drop-out rate.

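### HRSD change at week 4 and at week 6 are both primary, each tested at P<0.05 with no rule for combining them, while the sample size claims one 5% error at week 6 only

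*Protocol article*

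**What the plan says.** All references are to the protocol article.

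- **Outcomes:** this section states: "primary efficacy outcome is the change from baseline in mean total depression score using the 17-item version of the HRSD at weeks four and six". In the abstract (Methods/design) the same two time points appear: "17-item Hamilton Rating Scale for Depression after the fourth and sixth week of treatment". Neither place ranks them.
- **Statistical analysis, tests:** "The main statistical analysis will compare primary and secondary outcome measurements among groups at weeks four and six". The primary and the continuous secondary outcomes "among groups at baseline and weeks four and six, will be analyzed by one-way ANOVA". A one-way ANOVA compares the three arms at one visit, so this means a separate test per visit and not one model over time.
- **Statistical analysis, error level:** P<0.05 is the "level for all analysis". The only multiplicity device is the Bonferroni post-hoc step, and its stated purpose is the arms: this "test will be used to determine which means differ among the groups".
- **Sample size calculation:** the assumed advantage of 2.7 (SD 6.0) is in "HRSD score points after six weeks", with one 5% type 1 error, 83% power by F-test and 63 patients per group including 10% drop-out.

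No section names a principal visit, orders the tests, splits alpha between visits, or requires both visits to be significant.

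**The concern.** Two unranked primary time points, each tested at the full 5%, leave the definition of a positive trial open. If success at either visit is enough, the trial has two chances of a false positive and the single 5% error in the sample size section is not kept. If success is needed at both, the error is safe, but the power was computed for one test at one visit and does not carry over. The readings can give opposite conclusions from the same data, for instance when week 4 is significant and week 6 is not. Nothing in the article says which reading applies, so the choice could be made after the results are known.

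This is not something merely left to a fuller document. The article states the two time points, the common 0.05 level and the scope of the Bonferroni step, and those statements do not fit the single error rate it claims.

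**Working it through.** **Inputs from the article.** Three arms, 1:1:1; alpha 0.05 per test; difference 2.7 and SD 6.0, so d = 2.7/6.0 = 0.45; 63 per group less 10% drop-out, 63 × 0.9 = 56.7, taken as 57 evaluable per group (171 in total).

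**Input assumed.** The correlation ρ between HRSD change at week 4 and at week 6. The article gives none; 0 to 0.9 is shown.

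**Step 1. One visit.** Under no effect, a single F-test with 2 and 168 degrees of freedom (critical value 3.05) rejects in 5.0% of simulated trials, as claimed. For power, let both active arms beat placebo by d. The standardised spread of means is f = d × √2/3 = 0.45 × 0.471 = 0.212, and the noncentrality is 171 × 0.212² ≈ 7.7. This gives power of about 69%, not 83%. (The 63 per group is recovered only with f = 0.25: 57 × 1.10 ≈ 63. That is a separate sizing problem. It matters here only because 69% is the proper comparator in Step 4.)

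**Step 2. Either visit counts: error under no effect.** The ceiling for independent tests is 1 − (1 − 0.05)² = 9.75%. For correlated visits, two one-way ANOVAs with 57 per arm were simulated, at least 120,000 trials per value of ρ:

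| Assumed ρ | At least one F-test significant | F-test and a Bonferroni pair at the same visit |
|---|---|---|
| 0 | 9.7% | 8.2% |
| 0.5 | 9.2% | 7.7% |
| 0.7 | 8.4% | 7.2% |
| 0.8 | 7.8% | 6.7% |
| 0.9 | 7.0% | 6.0% |

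Repeat runs agree to within about 0.2 percentage points. Both columns exceed 5% throughout. The second is lower because Bonferroni over three pairs (0.05/3 each) is a further hurdle within a visit, but it does nothing across visits.

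**Step 3. Both visits required: error under no effect.** Both F-tests are significant in about 0.8% of trials at ρ = 0.5 and 2.1% at ρ = 0.8, so the error is well below 5%.

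**Step 4. Both visits required: power.** This needs a week 4 effect, which the article does not give; 2.7 points is assumed at both visits.

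| Criterion | One visit | Both, ρ = 0.5 | Both, ρ = 0.8 |
|---|---|---|---|
| Global F-test (both active arms better by d) | 69% | 54% | 60% |
| IHT better than placebo, Bonferroni | 49% | 32% | 39% |

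The one-visit pairwise figure can be checked by hand. The expected t is 0.45 × √(57/2) = 2.40 and the critical value at 0.05/3 two-sided is 2.42, so power is just under one half.

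**Step 5. Would splitting alpha work?** At 0.025 per visit the either-visit error is 4.6% (ρ = 0.5) to 4.1% (ρ = 0.8), so control returns. One-visit global-F power then falls from about 69% to about 59%.

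**The case against.** The strongest reply is that the article states no either-visit rule, so inflation is not a demonstrated property of the plan. That is right. A reader might infer that the trial's false-positive rate is 8–9%. The document does not support this as a flat statement: the figure needs an either-visit rule and an assumed correlation, and under a both-visits rule the error is below 5%. What remains is that no rule is given, and under neither reading do the stated 5% error and a power for one test at week 6 hold together.

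It is also fair that the aims are pairwise, so a claim for IHT or fluoxetine needs the Bonferroni step as well. On that criterion the excess is smaller, about 6–8% against 5%, but it does not vanish.

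Two further inferences should be resisted. Setting the 32–39% both-visit power against the planned 83% would blame this issue for too much: Bonferroni power for IHT versus placebo is already about 49% at one visit, and only the fall from there belongs here. And the Discussion's doubt about whether six weeks of IHT is long enough is no sign of a wish to favour week 4. It suggests that a longer course may be needed, which makes a benefit at week 4 alone less expected.

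Finally, the Blinding section keeps HRSD scores in closed envelopes and the statistician blinded to group identity until the end of the study. That guards against picking a visit on interim results, but not against picking one once the results are open. Sizing on six weeks hints that week 6 is the principal visit, but both places that define the primary outcome give the two visits equal standing.

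**Conclusion.** The point holds in conditional form. The plan has two unranked primary time points, a full 5% test at each, no adjustment or decision rule across them, and a sample size that rests on one of them.

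- **If either visit suffices,** the familywise error is about 7–10% for the global F-test and about 6–8% when a Bonferroni-significant pair is also needed, against a stated 5%.
- **If both are needed,** the error is below 5%, but global-F power falls from about 69% to about 54–60%, and Bonferroni power for IHT versus placebo from about 49% to about 32–39%.

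The error range rests on assumed correlations from 0 to 0.9. The power figures rest on correlations of 0.5–0.8, 57 evaluable per group and a 2.7-point effect at week 4 as well as week 6. The inflation is moderate, but it concerns the primary claim, and the open rule could decide the trial's conclusion.

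**What to change.** In Outcomes and in the abstract, name change from baseline in HRSD at week 6 as the single primary endpoint. In Statistical analysis, add that week 4 is a key secondary endpoint, tested at 5% only if the week 6 F-test is significant. This fixed order keeps the global F-tests over the two visits at 5% and matches the time point used for sizing. The Bonferroni step among the arms can stay as it is.

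The change takes a few sentences and no extra patients or visits. It should be dated and fixed before unblinding; the article was published in April 2013 with the study planned to end in December 2013, which leaves time. The cost is small: an effect seen only at week 4 can no longer be claimed as primary.

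Testing each visit at 0.025, or requiring both to be significant, would also control the error. Each costs power that the trial does not have to spare, and under either the power would have to be recalculated.
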